### **9.1.6 Criteria for assessing severity**

Severity of AEs will be assessed according to Good Clinical Practice (GCP) guidelines and NCI-CTCAE (V5) .

### **9.1.7 Criteria for assessing causality**

The site investigator will assess each AE for relatedness or causality of the intervention and the event. A guide to grading the degree of certainty about such a relationship is available at [https://www.who.int/medicines/areas/quality\\_safety/safety\\_efficacy/WHOcausality\\_assessment.pdf](https://www.who.int/medicines/areas/quality_safety/safety_efficacy/WHOcausality_assessment.pdf). A summary of the grading is as follows:

|                  |                                                                                      |
|------------------|--------------------------------------------------------------------------------------|
| Unrelated | Where the AE is clearly not related                                                  |
| Unlikely  | Where the AE does not have a clear relationship to the intervention                  |
| Possible  | Where the AE follows a known pattern of response                                     |
| Probable  | Where the AE reduces or ceases with withdrawal of the intervention                   |
| Definite  | Where the AE ceased with withdrawal of the intervention and recurs with re-exposure. |

As this study is blinded, all adverse and serious adverse events should be assessed for causal relationship assuming that the participant has been receiving anamorelin. When determining whether an AE or SAE is expected or not, please refer to the reference safety information provided in the Investigator Brochure. If the event is listed in the Investigator Brochure or specified as a symptom of special interest in section 9.1.9, the AE or SAE should be assumed to be 'Possible', 'Probable' or 'Definite' unless there is a clear alternative cause.

**Definite/Certain:** a clinical event, including laboratory test abnormality, occurring in a plausible time relationship to drug administration, and which cannot be explained by concurrent disease or other drugs or

chemicals. The response to withdrawal of the drug (dechallenge) should be clinically plausible. The event must be definitive pharmacologically or phenomenologically, using a satisfactory rechallenge procedure if necessary.

**Probable/Likely:** a clinical event, including laboratory test abnormality, with a reasonable time sequence to administration of the drug, unlikely to be attributed to concurrent disease or other drugs or chemicals, and which follows a clinically reasonable response on withdrawal (dechallenge). Rechallenge information is not required to fulfil this definition.

**Possible:** a clinical event, including laboratory test abnormality, with a reasonable time sequence to administrations of the drug, but which could also be explained by concurrent disease or other drugs or chemicals. Information on drug withdrawal may be lacking or unclear.

**Unlikely:** a clinical event, including laboratory test abnormality, with a temporal relationship to drug administration which makes a causal relationship improbable, and in which other drugs, chemicals or underlying disease provide plausible explanations.

**Conditional/Unclassified:** a clinical event, including laboratory test abnormality, reported as an adverse reaction, about which more data is essential for a proper assessment, or the additional data is under examination.

**Unassessable/Unclassifiable:** a report suggesting an adverse reaction which cannot be judged because information is insufficient or contradictory, and which cannot be supplemented or verified.

### ***9.1.8 Time period for assessing AEs and SAEs***

At each visit, the participants are encouraged to mention any problems since the last visit. In addition, the following standard questions should be asked:

- Have you had any medical problems since the last visit or study assessment?
- Have you started any new medications, other than given to you in this study, since the last visit or assessment?

For all randomised participants: all AEs, irrespective of causality, will be assessed and recorded as per ITCC SOP 5.17 Adverse Event Reporting. The time period includes the time from screening, the 12-week treatment period/the 4-week extension phase and the 4-week follow-up period (by telephone).

For patients who meet the eligibility criteria and then do not proceed to randomisation, any AEs detected during that window of time, should also be reported. If an AE is the reason that a person does not proceed to randomisation, this should be recorded within the eCRF, AE report and in the clinical record, irrespective of causality or seriousness.

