### **5.2.2 Safety Assessments**

Safety assessments are made at all participant contacts, before efficacy assessments. The following safety assessments will be obtained during the study:

1. physical examination (PE);
2. vital signs;
3. 12-lead electrocardiogram (ECG);
4. laboratory tests (hematology and blood chemistry);
5. documentation of adverse events (harms);
6. overall survival on all participants; and
7. tumour assessments using CT scans whenever they are done clinically using RECIST (response evaluation criteria in solid tumours) criteria.

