## 6.0 STUDY ASSESSMENTS

The study assessments are tabulated in Table 6-1. The study period will include 28 days after medication cessation (4 weekly follow-up period) or until death (whichever timeframe is shorter).

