b First telephone follow-up visit will occur 7 days after the Week 12 or Week 24 (if did not elect to enter extension) visit or the early termination visit due to withdrawal if treatment was ceased early. Subsequent telephone follow-up visits will occur every 7 days thereafter for a period of 4 weeks. There will be 4 follow-up visits in total.

Informed consent will be obtained prior to any study-related screening procedures.

ICECAP-A will be administered after the EQ-5D-5L questionnaire

\*Only if people elect NOT to enter the extension.

^ All electronically stored data from chest CT scans whenever they are done clinically will be used for evaluation of change in muscle mass at the thoracic (T4) level.

**Table 6-2** Schedule of Study Assessments for caregivers (Screening to Week 12 and optional extension – Weeks 13-24)

| Assessment                         | Patient screening | Baseline       | Visit Day Treatment Period |   |                 | Extension |                |
|------------------------------------|-------------------|----------------|----------------------------|---|-----------------|-----------|----------------|
| Week                               |                   |                | 4                          | 8 | 12              | 18        | 24             |
| Visit                              | 1                 | 2              | 3                          | 4 | 5               | 6         | 7              |
| Informed consent       | X                 | X ^ |                            |   |                 |           |                |
| EQ-5D-5L - quality of life         |                   | X              |                            |   | X* § |           | X § |
| Carer Experience Scale (CES)       |                   | X              |                            |   | X* § |           | X § |
| Diary (daily records by caregiver) |                   | X              | X                          | X | X               | X         | X              |

Informed consent will be obtained prior to any study-related procedures.

^OR (if consent not obtained during visit 1)

\*Only if patient elect not to enter the extension.

§ Or withdrawal

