### **8.13 Extension phase criteria**

At the end of the 12 weeks, participants are invited to enrol in an extension phase where they will continue to receive blinded intervention medication for another 12 weeks. The optional extension (for Weeks 13-24) is entirely based on participant's preference. During the extension phase frequency of AEs, quality of life, medication usage and compliance will be measured up to death or 28 days after ceasing study medication (whichever is the shorter period). These data will be collected via a weekly telephone call to the participant if they have been discharged home and recorded in the follow-up Data Collection Worksheet and eCRF as outlined above. The extension assessments outlined in Table 6-1 of study measures will also be completed.

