### **9.1.12      *Post study AEs and SAEs***

A post study event is defined as any event that occurs outside of the time period described in section 9.1.8 of the protocol. Investigators are required to report any events they become aware of if:

- the event occurs at any time after study participation has ceased; and
- the event is assessed as being reasonably related to the study intervention.

Investigators are not obliged to actively seek events that occur after the study period defined in 9.1.8. Date of death will be required for all participants regardless of when they withdrew from the study up to the dataset being closed.

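### Section 9.1.8 counts a 4-week extension where the extension lasts 12 weeks, so its AE/SAE period omits 8 weeks for extenders; separately, extension drug is scheduled for Week 18 instead of Week 12

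*Supplement*

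**What the plan says.** **AE/SAE period.** Section 9.1.8 states: "The time period includes the time from screening, the 12-week treatment period/the 4-week extension phase and the 4-week follow-up period (by telephone". Section 8.13 says of participants who extend that "they will continue to receive blinded intervention medication for another 12 weeks", and section 3.1 numbers those weeks 13 to 24. Section 8.13 also has AE frequency "measured up to death or 28 days after ceasing study medication (whichever is the shorter period". Section 6.0 ties follow-up to the end of drug: "The study period will include 28 days after medication cessation (4 weekly follow-up period". Footnote b of Table 6-1 ties it to the final visit: "First telephone follow-up visit will occur 7 days after the Week 12 or Week 24".

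Section 9.1.12 builds on 9.1.8: "A post study event is defined as any event that occurs outside of the time period described in section 9.1.8 of the protocol". It adds: "Investigators are not obliged to actively seek events that occur after the study period defined in 9.1.8".

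**Extension supply.** Section 4.2 gives two supply points, one after randomisation and one at Week 18. The dispense/return row of Table 6-1 agrees: dispense at baseline, return at Week 12, dispense at Week 18, return at Week 24. Section 4.2 also requires daily dosing up to Week 24 for those who extend. Section 4.6 sets the kits at 90 tablets for the first 12 weeks and 80 for the extension. Section 4.7 has unused drug returned after the last dose and compliance checked at Week 18. The Week 12 opt-in list in 7.5 covers home delivery of medication. The Week 18 list in 7.6 has a compliance check but no dispensing item.

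**The concern.** Safety is part of the primary objective, and the section that defines the AE/SAE period disagrees with the rest of the protocol about how long an extender is on treatment. Read literally, some events that occur on drug fall outside the period. Because 9.1.12 refers back to 9.1.8, those events would carry the post-study label and would not need to be actively sought, while 8.13 requires AEs to be measured until 28 days after the last dose. A site or safety reviewer could defend either reading.

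The supply slip is unrelated in origin but touches the same participants. The two places that state when extension drug is dispensed agree with each other on Week 18, six weeks after the extension begins. If a site or the pharmacy acted on them, blinded treatment would be interrupted for much of the extension. The 24-week data, which are meant to describe longer treatment, would then describe an interrupted course.

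**Working it through.** **Inputs**

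| Quantity | Value | Source |
|---|---|---|
| Extension in the AE/SAE period | 4 weeks | 9.1.8 |
| Extension as designed | Weeks 13-24 | 3.1, 8.13 |
| Main treatment | 12 weeks | 3.1 |
| Telephone follow-up | 4 weeks | 9.1.8, Table 6-1 footnote b |
| First kit / extension kit | 90 / 80 tablets | 4.6 |
| Dose | 1 tablet daily | 4.2 |
| Extension dispensing | Week 18 | 4.2, Table 6-1 |

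**1. AE/SAE period**

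Extension length: 24 - 13 + 1 = 12 weeks. The 4 weeks in 9.1.8 cannot be reproduced. It is not the follow-up under another name, because the same sentence counts the 4-week follow-up separately.

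Shortfall: 12 - 4 = 8 weeks. Which 8 depends on where follow-up starts.

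- *Follow-up starts at cessation or the final visit (6.0, Table 6-1 footnote b).* Named on-drug weeks are 12 + 4 = 16. Weeks 25-28 are covered as follow-up. Weeks 17-24 are omitted: all 8 are on drug, and they contain both extension visits (Weeks 18 and 24).
- *Blocks run consecutively as listed in 9.1.8.* 12 + 4 + 4 = 20 weeks, against 12 + 12 + 4 = 28 needed. Weeks 21-28 are omitted: 4 on drug and 4 of follow-up.

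Weeks 21-24, all on drug, are omitted on either reading. The first reading fits the rest of the protocol better.

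**2. Extension supply, read literally**

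Conventions: Week n is Day 7n, no doses are missed, and the first dose from a new kit is taken the day after supply.

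- Extension days: 85 to 168, so 84 doses.
- Left over from the first kit at Week 12: 90 - 84 = 6 tablets, which last to Day 90.
- Week 18 is Day 126. Days without drug: 91 to 126, so 126 - 90 = 36 days; 36/84 = 43%.
- If leftovers are returned at Week 12, as Table 6-1 marks: days 85 to 126, so 126 - 84 = 42 days; 42/84 = 50%.
- Doses remaining after Week 18: 168 - 126 = 42. An 80-tablet kit would leave 80 - 42 = 38 unused.

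**3. Same kit dispensed at Week 12**

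- Leftovers kept: 6 + 80 = 86 tablets for 84 days, 2 to spare.
- Leftovers returned: 80 tablets for 84 days, 4 short.

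The 80-tablet kit therefore fits Week 12 supply with leftovers retained, and does not fit Week 18 supply. The opt-in delivery item in 7.5, the Week 18 compliance check and the missing dispensing item in 7.6 all point the same way.

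**The case against.** The strongest reply is that 9.1.8 contains a slip with no effect on data collection. Its opening lines have participants asked at each visit about medical problems since the previous one, and asking this at Weeks 18 and 24 covers the whole extension. Its list of periods is introduced by a verb that need not be exhaustive. Section 5.2.2 says "Safety assessments are made at all participant contacts, before efficacy assessments". The Harms row of Table 6-1, the Week 18 and Week 24 visit lists and section 8.13 all collect AEs. The reporting conditions in 9.1.12 apply only once participation has ceased, so they do not release anyone from reporting an on-drug event. All of this stands, and it limits the first item to a definition that needs correcting. It does not remove the contradiction, because 9.1.12 still points to 9.1.8 for its boundary.

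On supply, the reply is that the documents resolve the matter themselves. Drug is dispensed on prescription and sent to the home (4.6), so a visit column does not by itself trigger a shipment. The Week 12 list covers delivery. The amendment listing explains the kit sizes by reference to the Week 12 decision on the extension. The pharmacy manual is not available here and may already say Week 12. This also stands as a reason to treat the 36- and 42-day gaps as worst cases resting on exact visit days and full adherence. But an inference from several sections should not have to override an explicit statement in 4.2 that the schedule table repeats.

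Finally, the two slips are separate, the extension is optional, its 24-week analyses are exploratory, and the Week 12 analyses are untouched. Those points are accepted.

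**Conclusion.** Both statements are wrong as written. The AE/SAE period in 9.1.8 is 8 weeks short for extenders: Weeks 17-24 with follow-up anchored to cessation, Weeks 21-28 if the blocks run consecutively, and Weeks 21-24 in either case. The consequence is a contradictory definition that 9.1.12 inherits; scheduled harms collection continues.

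Extension dispensing at Week 18 contradicts continuous dosing, the return rule, the kit size and the visit lists. Taken literally it leaves 36 of 84 days (43%) without drug, or 42 (50%) with a Week 12 return, under the day-count conventions stated above. Week 12 supply was evidently intended.

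This should be fixed, and mainly because of the supply schedule; the AE/SAE item alone is a wording correction. The 8-week figure rests only on protocol durations. The supply figures describe what happens if the text is followed literally and do not predict what sites will do.

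**What to change.** - **9.1.8:** replace the 4-week extension with a 12-week extension phase (Weeks 13-24), and state that the 4-week telephone follow-up starts at drug cessation, as in 6.0. This also corrects 9.1.12 without further change.
- **4.2 and Table 6-1:** move extension dispensing from Week 18 to Week 12.
- **Table 6-1:** limit the Week 12 return to participants who do not enter the extension, in line with 4.7. If a Week 12 return is kept for everyone, raise the extension kit to at least 84 tablets.
- **Pharmacy manual:** check that it gives Week 12 for extension supply.

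The cost is a wording amendment in three places and one check of the manual. No visits or data are added.

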#### **9.1.9      *National Cancer Institute, Common Terminology Criteria for Adverse Events. (NCI CTC AE).V5.0***

These criteria have been used to determine AEs likely to occur during the study period and will be used to determine AE reporting and study progress. Criteria specific to the expected events known to be associated with anamorelin have been listed. This is administered by study staff.

Symptoms will be identified during each visit using criteria established by the National Cancer Institute, and will be graded accordingly. Specifically, for this study, the symptoms of interest will be:

- Symptomatic hyperglycaemia (dizziness, cold sweat, loss of consciousness, abdominal pain, shortness of breath, confusion), constipation, nausea, vomiting.
- Blood glucose increased (investigation)
- Symptoms of cardiac dysfunction (PR prolongation and increased QT interval measured on ECG), blurred vision, breathlessness, chest pain, syncope, palpitations
- Headache
- Peripheral oedema

A grade of 3 (that has not responded to symptomatic treatment instituted by the treating physician according to local protocols) or 4 will activate cessation of study intervention and an SAE report. All AEs will be collated by the project officer and reported to the executive committee on a monthly basis. AE rates will form part of the Key Performance Indicators for the study and will be reported on a regular basis to the Trial Steering Committee and the ethical review boards of the participating sites.

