## 1.5 Relevant safety and toxicity information

The current safety profile of anamorelin was established from the ROMANA trials. The most common drug-related treatment emergent harms observed were diabetes and hyperglycaemia, occurring in <1% of patients in ROMANA1 and ROMANA 2 trials. Anamorelin also induced prolongation of PR and QRS intervals at supratherapeutic doses of 300 and 400mg (based on 24-hour Holter monitoring data from Study HT-ANAM-112). The electrocardiogram (ECG) effects were then reassessed in a thorough QT/QTc study (Study HT-ANAM-113) which confirmed that anamorelin had no meaningful effect on ventricular repolarization. All ECG changes were transient, and none of the QT prolongations were above an absolute value of 450ms or were an increase of >60ms from baseline. Other associated harms were nausea, diarrhea, peripheral oedema and fatigue. In view of this, this study will specifically seek evidence of cardiac dysfunction, symptomatic hyperglycaemia, drug interactions, constipation, nausea and vomiting using National Cancer Institute Common Terminology Criteria for Adverse Event (NCI-CTCAE) gradings. Importantly, this proposed trial is using a dose of 100mg which has not been clinically associated with cardiac dysfunction.

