|  | 
pre-existing diabetes mellitus an assessment of the individual benefit-risk balance should be performed.
 
Hepatic impairment: Anamorelin should be used with caution in patients with mild to moderate hepatic impairment as its use in patients with hepatic impairment may be associated with increased exposure to anamorelin.
 
Contra indications:
 
Interactions with CYP3A4: Co-administration of anamorelin with medicinal products that inhibit (e.g ketoconazole, clarithromycin, erythromycin, diltiazem, itraconazole, ritonavir, verapamil) or induce (e.g. rifampicin) CYP3A4 activity may affect anamorelin plasma concentrations. Concomitant administration of anamorelin with strong CYP3A4 inhibitors should be avoided and the concomitant use of anamorelin with moderate CYP3A4 inhibitors should be done with caution. Concomitant administration of anamorelin with strong CYP3A4 inducers should be done with caution.
 
Food effect: Food decreases anamorelin bioavailability and consequently anamorelin should be taken on an empty stomach at least one hour before a meal.
 
Cardiac effects: Anamorelin induced prolongation of PR and QRS intervals at supra-therapeutic doses. Therefore, anamorelin should be used with caution in the case of co-administration of medicinal products that may increase its exposure such as antiarrhythmic medications Class I (fast sodium (NA) channel blockers (e.g. quinidine, disopyramide, procainamide, lidocaine, phenytoin, flecainide, propafenone).
 |

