**Vital signs** including body temperature (°C), blood pressure (mmHG, systolic and diastolic), respiratory rate (breaths per minute) and heart rate (beats per minute) will be measured as part of the safety assessments at every visit: screening (Visit 1) and at Weeks 4, 8 and 12 (Visits 3, 4 and 5) as well as during optional extension phase at Weeks 18 and 24 (Visits 6 and 7). Pulse rate, systolic and diastolic blood pressure will be measured after the patient has been resting in the semi-supine position for at least 5 minutes.

A **complete medical history** will be recorded at the screening visit (Visit 1) and will include evaluations for past or present conditions. **Concomitant medications** will also be recorded at every visit: screening (Visit 1), baseline (Visit 2) and at Weeks 4, 8 and 12 (Visits 3, 4 and 5) as well as during optional extension phase at Weeks 18 and 24 (Visits 6 and 7).

**12-lead ECGs** will be conducted at screening (Visit1), Weeks 4, 8 and 12 (Visits 3, 4 and 5). Any new or worsening ECG abnormalities assessed to be clinically significant by the study investigator will be reported as adverse events. When possible, ECG will be recorded at 1 hour ( $\pm 5$  minutes) post dose to align with occurrence of Cmax. At screening visit ECG will be taken pre-dose (as no dose will be administered at this time).

**Short Blessed Test** will be administered at screening to assess cognitive capacity and will assist the PI to assess eligibility by determining the persons capacity to understand the study and to complete the assessments. A score of 10 or more is required.

**Adverse event assessment** the research team member who sees the participants and their caregivers will also ask about any other unexpected adverse outcomes. The study investigators will oversee the research team members. All serious adverse events will be reported in accordance with the requirements of the approving central Research and Ethics Committee as defined in the committee's safety reporting standard operating procedures (see section 9.1 Adverse Events). Serious adverse events will be followed until documentation of resolution or the successful initiation of relevant management strategies. Other adverse events will be described in the Annual Report to the Committee.

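### The section 9.1.9 list of ECG events of interest names PR and QT but not QRS, which does not match the protocol's own account of the drug's ECG effect

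*Supplement*

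**What the plan says.** Section 9.1.9 describes its own scope: "Criteria specific to the expected events known to be associated with anamorelin have been listed". Events are to be identified and graded at each visit, and the cardiac line is "Symptoms of cardiac dysfunction (PR prolongation and increased QT interval measured on ECG), blurred vision, breathlessness, chest pain, syncope, palpitations".

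The background in section 1.5 states the ECG effect differently: "Anamorelin also induced prolongation of PR and QRS intervals at supratherapeutic doses of 300 and 400mg". It then cites a thorough QT study "which confirmed that anamorelin had no meaningful effect on ventricular repolarization", and adds that no QT prolongation went above 450 ms or rose by more than 60 ms. Table 4-1 repeats the conduction effect: "Anamorelin induced prolongation of PR and QRS intervals at supra-therapeutic doses". Exclusion criterion 11 bars regular use of drugs that may lengthen PR or QRS. Table 3-1, listing the same drug class for screening staff, gives PR or 'QTS'.

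The list carries weight elsewhere. Under section 9.1.7 an event that is in the Investigator Brochure, or "specified as a symptom of special interest in section 9.1.9", is presumed at least possibly related unless another cause is clear.

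On timing, section 5.2.2 opens with "Safety assessments are made at all participant contacts, before efficacy assessments" and includes the 12-lead ECG in the list that follows. Section 6.2 and Table 6-1 place ECGs at screening and Weeks 4, 8 and 12. Table 6-1 adds one in the Exit/Early Termination column. Neither Table 6-1 nor sections 7.6 and 7.7 show an ECG at Week 18 or Week 24.

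**The concern.** A list that claims to cover the drug's known events should match the drug profile given in the same document. Here it takes in the interval for which 1.5 reports no meaningful effect and leaves out one of the two it reports as prolonged. Safety is part of the primary objective, and 1.5 commits the study to looking specifically for cardiac dysfunction.

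The omission matters because of how ECG findings become data. For an interval that is not named, the working route is section 6.2, which turns an ECG change into an adverse event only if the investigator considers it clinically significant. A modest QRS change that no one flags would not appear among the adverse events. With 50 participants randomised 1:1, so 25 per arm, counts of flagged events will be small in any case. The measured intervals are the more informative record for a phase III decision.

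**Working it through.** No arithmetic beyond counting applies; the check sets the passages side by side.

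**Which intervals each place names**

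| Place | PR | QRS | QT |
|---|---|---|---|
| 1.5, drug effect at 300 and 400 mg | yes | yes | no meaningful effect on repolarisation |
| Table 4-1, cardiac warning | yes | yes | not named |
| Exclusion criterion 11 | yes | yes | not named |
| Table 3-1, same drug class | yes | entry reads 'QTS' | entry reads 'QTS' |
| 9.1.9, events of interest | yes | **not named** | yes |

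Of the two intervals in the stated effect, 9.1.9 has one (PR) and lacks one (QRS). The protocol gives no reason for leaving QRS out. The 'QTS' entry in Table 3-1, beside PR or QRS in criterion 11, suggests a drafting slip between QRS and QT rather than a choice, though the text cannot prove that.

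**What a QRS change still triggers without being listed**

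- *Recording.* Section 6.2 makes any ECG abnormality an adverse event once the investigator finds it clinically significant. Section 9.1.8 has all adverse events recorded whatever their cause.
- *Cessation.* Section 4.8 covers side effects of study medication at grade 3 that persist despite treatment, and all at grade 4 or 5. Section 8.10 applies a similar trigger to adverse events generally. Neither is confined to the 9.1.9 list.
- *Causality default.* Section 9.1.7 has two routes, the Investigator Brochure or the 9.1.9 list. The warnings row of Table 4-1, which holds the PR and QRS statement, cites reference 18, and reference 18 is the Investigator Brochure. QRS may therefore qualify by that route. The brochure is not supplied, so this cannot be confirmed.

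**What it lacks**

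- Explicit naming for identification and grading at visits under 9.1.9.
- The list route to the causality default in 9.1.7.
- Arguably, the serious-adverse-event report that 9.1.9 attaches to its grade trigger; 8.10 asks only for an adverse-event report.

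**ECG timing**

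Scheduled extension visits: 2 (Weeks 18 and 24). ECGs listed at them: 0. Table 6-1 has an ECG in the exit column, and its footnote places that visit after the last dose, which on its face includes people who finish the extension. Section 8.10 points the same way: it has the Week 12 measures taken at end of treatment, and those include an ECG. Section 7.7 lists none for Week 24. Read together, an extension participant has an ECG at Week 12 and one at exit, with none shown between. The wording in 9.1.9 about each visit does not fit that.

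**The case against.** The strongest reply is that little depends on the list. PR, half of the stated conduction effect, is on it, as are syncope, palpitations, chest pain and breathlessness. General rules catch a QRS change that the investigator considers important, and the brochure probably supplies the causality default. Section 9.1.9 itself has all adverse events collated, and section 10.4 summarises all safety data; no separate report confined to listed events is described. The effect was reported at 300 and 400 mg, whereas this trial uses 100 mg, a dose that 1.5 says has not been clinically linked to cardiac dysfunction. Most of this stands, and it limits the consequence. It does not remove the mismatch between 9.1.9 and three other places.

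The dose argument is incomplete. Table 4-1 bases a caution on the PR and QRS effect for co-medication that may raise exposure, and says hepatic impairment may raise exposure too. The interval therefore remains relevant on the protocol's own account.

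On timing, 5.2.2 can fairly be read as saying that some safety assessment happens at every contact, followed by a list of what is obtained over the study. That list includes CT scans done only when clinically ordered, and contacts include telephone calls. This reading is reasonable, so the point is one of reconciliation.

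A reader might infer more than the text supports:

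- That the drug's known cardiac effect falls outside the special-interest rules altogether. It does not; PR is listed.
- That listing QT is a mistake. Section 1.5 says no meaningful effect and still speaks of QT prolongations, so watching QT is defensible.
- That half of the 24 treatment weeks go without cardiac monitoring in the extension. That counts calendar weeks rather than missed assessments and ignores the Week 12 and exit ECGs.

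**Conclusion.** The inconsistency is real and can be read directly from the protocol: 9.1.9 omits QRS, although 1.5 and Table 4-1 name it with PR as the drug's ECG effect and criterion 11 uses the same pair. Its size is one interval of two left unnamed. QRS is still monitored through the general rules, but a change that is not judged clinically significant could go unreported. This does not undermine the trial, but it should be corrected because safety is a primary aim and the correction is cheap.

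Two things remain unknown: whether the Investigator Brochure lists QRS prolongation in its reference safety information, and whether the eCRF already captures numeric intervals. Section 9.4.3 names ECG among the recorded measures without saying in what form. No separate analysis plan is shown, so the absence of an ECG table is not counted as a fault.

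The extension schedule is a lesser, separate mismatch of wording.

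**What to change.** 1. Reconcile the ECG items in 9.1.9 with section 1.5, exclusion criterion 11 and Table 4-1, and correct 'QTS' in Table 3-1 to agree. QT may stay. If QRS is left out deliberately, give the reason. Any clinical action that follows an ECG change is for the sponsor's clinical team to settle.
2. Summarise PR, QRS and QT by arm, as values and as change from screening, using the ECGs already scheduled. This makes the QRS evidence independent of whether an investigator flags a finding.
3. Reconcile 9.1.9 and 5.2.2 with 6.2, 7.6, 7.7 and Table 6-1, so that the text and the ECG schedule for Weeks 18, 24 and exit agree.

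The cost is a few lines of protocol text and, if the values are not already captured, three numeric fields per ECG. The downside is slightly more data entry. No extra ECG is needed for items 1 and 2.
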